This is a within-subjects design measuring: (1) youth brain response to their own change language during group MI, (2) youth brain response to peer-peer dyadic exchanges during group MI (specifically, to peer language), and (3) how brain response is associated with youth behavior change at 3-, 6-, and 12-months post-treatment. Within this study, two U-EAs engaged in hazardous drinking will be scheduled to attend a “Participation Day,” comprised of a baseline behavioral assessment (which they will complete alone), a single 1-hour session of virtual group MI (completed together), and to ensure maximum salience of the peer dyadic experience, the fMRI scanning protocol on the afternoon of the same day (completed simultaneously). To determine how these factors relate to alcohol-related behavior change, youth will complete behavioral follow-ups at 3-, 6-, and 12-months post-intervention.

1. Study Population
2. Number of Subjects

N = 248 youth.

1. Inclusion and Exclusion Criteria

Inclusion criteria

For inclusion, youth must be: (1) 18-19 years of age; (2) agree to be contacted for the 3, 6, and 12 month follow ups; (3) provide fully informed consent.

Exclusion criteria

With respect to the fMRI component, we have attempted to maintain tight control over factors that may increase error variability and that maximize protection for our participants. Thus, our exclusion criteria are: (1) left-handed; (2) evidence of brain injury/illness and/or neurological, neurodevelopmental disorder including psychosis and related medications (e.g., antipsychotics; neuroleptics); (3) loss of consciousness ≥ 2 minutes; (4) other fMRI contraindications (e.g., unremovable metal on/in body, pregnant)

1. Vulnerable Populations

This study will not enroll any vulnerable populations.

1. Setting

We will employ community and campus recruitment methods across the greater Dallas, Texas metro area to recruit a sample with sufficient hazardous drinking to assess mechanisms underlying behavior change within this group MI intervention. In-person study procedures (Participation Day) will take place at the University of Texas Dallas (UTD) in private, dedicated rooms in the Center for BrainHealth and adjacent spaces assigned to the UTD team for this purpose. Follow ups (at 3-, 6-, and 12-months) will be conducted virtually using a secure online data collection system (REDCap), and will include a brief online or telephone interview with UTD project staff.

1. Recruitment Methods

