Study team members will check in with participants prior to beginning the baseline procedures to ensure that participants understand the study details and their rights as participants. Research staff will reiterate the voluntary nature of all aspects of the study, and participants’ right to refuse to answer any questions with which they are uncomfortable and/or to withdraw from the study at any time without any type of recrimination.

Eligible U-EA will be invited to complete consent forms on paper during their participation day, which we have found increases accessibility in the consent process. This system allows the participant to review the entire consent form, discuss the study and have questions answered with a UTD study team member, allows UTD study team member to ensure participants understand the consent form, and complete the form if they consent to participate.

1. Procedures

**Participation Day Procedures (#1-3 below)**. Our UTD team will keep a rolling list of eligible participants. After two same-sex U-EA have been deemed eligible and consented, our team will contact youth to ensure that there is no change in their eligibility (if more than 30 days have passed since screening) and they will then be scheduled in dyads for “Participation Day” activities, which include the baseline assessment (which they will complete alone), the group MI (completed together virtually with a URI study counselor), and the scan (completed simultaneously). We will ensure that U-EA are able to participate on the same day, including completing the baseline assessments at the same time, the group MI together, and then the scan simultaneously on the same afternoon. All intervention groups will be stratified by biological sex (e.g., male, female). This is commensurate with our approach with other group MI protocols with this age group [97-99]. To improve accessibility, all Participation Day components, including the assessment and the group MI, will be delivered in private, dedicated rooms in the Center for BrainHealth and adjacent spaces assigned to our UTD team for this purpose.

- - 1. Biohazards and TimeLine Follow Back.

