Primary Measures. In line with our prior studies [2, 3, 59-61], at the start of the Participation Day, youth will be breathalyzed using a BACtrack S80 Professional Breathalyzer to ensure BAC=0. Consistent with the PI’s prior translational work [2, 3, 59-61], all participants will be required to abstain from alcohol and other substances for 24 hours prior to the scan. Upon arrival to the Center for BrainHealth, youth will be screened to assure the absence of fMRI contraindications (no metal in body; not pregnant as verified by urine testing for all female participants; breath alcohol = 0). Only approved youth will be scanned. Our primary outcomes include two variables: alcohol use days and hazardous drinking. We will utilize the TimeLine Follow-Back [TLFB; 172], a calendar-based measure which provides quantity and frequency of past 30 day substance use (including alcohol use days), and has been validated on internet-based platforms [173]. This measure will also provide rates of cannabis and other substance use (e.g., e-cigarette/vaping; prescription opioid use). The second primary outcome of hazardous drinking will be will be assessed following the virtual group MI session via Rutgers Alcohol Problems Index [RAPI; 174].

- - 1. Virtual Group MI Session. In line with our previous group MI approaches to reduce alcohol and related health risk behavior with this age group, all participants will receive 1 60-minute group MI session conducted virtually by a graduate Clinical Psychology PhD student or postdoctoral researcher affiliated with PI [name]’s ANCHoR team and will proceed according to our established group MI manual for U-EA alcohol use [89]. This group MI aims to introduce a conversation about alcohol use and the personally experienced consequences of hazardous drinking [2, 87, 90, 92, 96-100]. Group MI interventionists will conduct the MI in an MI-consistent manner, meaning that they will be open, strength-based, affirming, non-judgmental, and empathic, with a goal of reducing resistance and highlighting ambivalence around hazardous drinking to foster and support U-EAs’ intrinsic motivation for behavior change.

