Following our empirically-supported approach for MI targeting alcohol use with non-treatment-seeking youth, the group MI will start with an open-ended exploration of dyad’s hazardous drinking behavior via eliciting the dyad’s stories about their alcohol use. Following this open-ended exploration, group MI interventionists will guide the youth through a values clarification task [186]. The remainder of the group MI will focus on providing age-matched norms from this geographic region (Texas), and an averaged overview of personalized feedback regarding the dyad’s alcohol use (as derived from their baseline assessment data). Following this, the group MI interventionist will actively and collaboratively engage the dyad in the development of discrepancy (exploring how their drinking fits with their immediate and long-term goals), the identification of high-risk situations (e.g., sports events; going to parties; hanging out with certain friends who tend to drink heavily) and triggers for drinking (e.g., feelings of sadness; anxiety; celebration), and an exploration of strategies to manage those risks and triggers to help the dyad reduce their hazardous drinking in those contexts. The ultimate goal of the group MI session is to engage the dyad in a thoughtful conversation about their hazardous drinking and the implications that their hazardous drinking may have on their lives, with an eye to bolstering and supporting the dyad’s inherent drive for behavior change. The group MI interventionist will close with a summary of the session and a broad and non-judgmental query of how the dyad would like their alcohol use to be in the near future (e.g., “Tell me how you would like your drinking to look when our team talks with you in 3 months.”)

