Assurance of Intervention Fidelity. To ensure intervention integrity and fidelity, all group MI sessions will follow our group MI manual [89]. This group MI was developed based on the PI’s clinical work with youth engaged in alcohol and other substance use and continues to be updated in line with recent publications in the MI field [57, 58, 89, 90, 96, 98, 99, 116-136]. The PI is a recognized expert in training and conducting MI and group MI with youth. In line with her previous NIH-funded studies, she will train each group MI interventionist via the following 5 steps. Group MI interventionists will: (1) receive didactic training on the theories behind group MI, (2) be required to read the group MI study manual, (3) pass a knowledge test to evaluate their grasp of the concepts within and behind group MI (e.g., with a pass rate of at least 80% on the fidelity checklist and 100% adherence to essential therapeutic elements), (4) watch the PI conduct a pilot group MI and discuss the details of the session, and (5) conduct two pilot group MIs, which will be observed by the PI who will assess the group MI interventionist’s proficiency in the manualized group MI intervention. All sessions will be audio-recorded for the purposes of systematic supervision, allowing PI [name] to ensure fidelity and prevent therapist drift. If a group MI interventionist is found to have lower levels of intervention integrity or significant drift, the PI will provide the group MI interventionist with feedback and training until they are back on track.

- - 1. Baseline Behavioral Assessment. Our team has moved to REDCap for our current NIH-funded studies [2, 169], which has gained support as a user-friendly, reliable, and secure way to obtain survey data, including health risk behavior with this age group [170, 171]. Each member of the U-EA dyad will complete behavioral assessments using REDCap via lab computers in separate rooms after their participation in the virtual group MI. All questionnaires will be self-reported from the participant. All measures are taken by the participant with no assistance from study personnel.

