Primary Measures. Our Demographic questionnaire collects age, self-identified gender, race/ethnicity, education, income, parent education, family income, and related information. The RAPI will be during this baseline behavioral assessment to collect hazardous drinking patterns. In terms of relevant youth and peer factors that may be salient to intervention outcomes, U-EAs will complete the UCLA Lonelinesss Scale, the personal responsibility subscale of the Psychosocial Maturity Inventory [176], the Perceived Discrimination Scale, the Pittsburgh Sleep Quality Index, and the Prosocial Subscale from within the Strengths and Difficulties Questionnaire (SDQ) [178] [179, 180]. Additional health risk behavior will be evaluated with the Sexual Behavior Questionnaire. The SBQ will be a requirement due to the co-occurrent behavior that could stem from alcohol use. We will evaluate alcohol use disorder symptoms via the DSM-5 alcohol use disorder criteria [84], and assess cannabis use impairment and symptomatology via the Cannabis Problems Questionnaire and the DSM-5 cannabis use disorder criteria. Immediately post-scan, we will query youth’s level of agreement with the presented statement [182] presented in the fMRI (NILE) paradigm via likert scale.

- - 1. Neuroimaging Session. We will conduct the fMRI session in the afternoon of the “Participation Day” to maximize salience of the peer interaction from the group MI. Between the virtual group MI and scan session, in line with our previous youth translational approaches [2, 3, 59-61], the PI’s team will capture audio recordings of salient peer change talk from the peer health session to integrate into the dyads’ individualized fMRI task (see Figure 6 and our team’s coding experience for details). Scanning will take place at the Center for BrainHealth.

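### The only baseline RAPI, a declared primary outcome, is placed after the group MI session, against the order given in the protocol's own overviews

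*Protocol*

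**What the plan says.** Under Procedures (Biohazards and TimeLine Follow Back, Primary Measures) the protocol states: "Our primary outcomes include two variables: alcohol use days and hazardous drinking". Drinking days come from the TLFB, which belongs to this first item of the day. For the other outcome the same paragraph says: "The second primary outcome of hazardous drinking will be will be assessed following the virtual group MI session via Rutgers Alcohol Problems Index".

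The later item, Baseline Behavioral Assessment, has each dyad member complete the REDCap questionnaires "in separate rooms after their participation in the virtual group MI". Its own Primary Measures paragraph puts the RAPI in that battery: "The RAPI will be during this baseline behavioral assessment to collect hazardous drinking patterns". The battery also holds the DSM-5 alcohol and cannabis use disorder criteria, the Cannabis Problems Questionnaire and several psychosocial scales.

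Two overview passages give a different order. Study Design describes a day "comprised of a baseline behavioral assessment (which they will complete alone), a single 1-hour session of virtual group MI (completed together"), followed by the scan. The Participation Day overview under Procedures speaks of "including completing the baseline assessments at the same time, the group MI together, and then the scan simultaneously on the same afternoon". Under Virtual Group MI Session, the feedback given in the session is described "as derived from their baseline assessment data".

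**The concern.** A baseline for judging response to an intervention should precede it. Here the form called baseline is completed after the intervention has been delivered in full, and the session covers much the same ground as an alcohol problems index: the participants' drinking stories and the consequences they have met. One hour cannot alter past problems, but it can alter how they are recalled and reported.

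The study is single-group and within-subjects, so no comparison arm carries the same shift and cancels it. The follow-up questionnaires are completed remotely, with no session just before them, so the baseline and follow-up RAPI would also be collected under different conditions. Once a participant has passed through the day in this order, no analysis can recover the missing pre-session value. The same holds for the alcohol and cannabis symptom measures in the battery.

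Staff also cannot follow both orders as they stand.

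**Working it through.** No figure in the plan has to be reproduced; the check is a comparison of texts.

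| Place in the protocol | Order given | How explicit |
|---|---|---|
| Study Design | baseline assessment, MI, scan | by order of listing; the scan is set in the afternoon |
| Procedures, Participation Day overview | baseline assessments, MI, scan | by listing; an explicit *then* only before the scan |
| Procedures, Biohazards and TimeLine Follow Back | breath test and TLFB first; RAPI after MI | explicit for the RAPI |
| Procedures, Baseline Behavioral Assessment | whole battery, RAPI included, after MI | explicit |

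1. *Is the RAPI a primary outcome?* Yes, by the Primary Measures paragraph, as the second of two.
2. *Is there another RAPI before the session?* None is described. The TLFB yields quantity and frequency of use, not problems. The remaining RAPI occasions are the follow-ups at 3, 6 and 12 months.
3. *Is a baseline RAPI meant to be used?* The third objective is behavior change. Follow-up Measures repeats the baseline package at each follow-up. The opening of Data Analysis lists behavioral data from baseline together with 3, 6 and 12 months as the source of measures. No RAPI analysis is written out.
4. *What would a reporting shift do?* Let B be the score a participant would have reported before the session, s the shift in reporting caused by the session, and F the score at follow-up. The recorded baseline is B + s, so the recorded change is F − (B + s) = (F − B) − s. The mean change is wrong by exactly the mean of s, with opposite sign. If discussing problems raises reporting (s > 0), later improvement looks larger than it was; if it lowers reporting (s < 0), improvement is hidden. The document gives no value and no sign for s.
5. *What is not touched?* The TLFB stands in the first Procedures item, ahead of the MI item, so baseline drinking days read as pre-session. The linear mixed-effects model under Behavioral analyses has TLFB drinking days as its outcome, at 3, 6 and 12 months. It does not use the RAPI.

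**The case against.** **The analysis does not use this value.** The only model described concerns TLFB drinking days; no RAPI change score or baseline adjustment is specified. This is correct and limits the reach of the point. It does not dispose of it: the RAPI is still declared primary, and baseline behavioral data are still named as an analysis source.

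**The contradiction is softer than it looks.** The overviews list components, while the detailed items are explicit and agree with each other. The split between TLFB first and battery later may be deliberate, with overview text left behind. That is plausible. But a deliberate order still leaves a post-session form labelled baseline.

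**The RAPI is answered privately.** Participants complete it alone, on a computer, without staff help. This stands, and weakens any argument from the presence of a peer or counselor. It does not remove the effect of the preceding conversation on recall.

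**Asking first has its own cost.** Problem questions just before the session could prime the change talk that is extracted for the scanner task. This stands and belongs in the cost of the fix.

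A reader might infer three stronger things, none of which the document supports:

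- *That the session feedback could not be prepared.* The feedback concerns the dyad's alcohol use, and the pre-session TLFB can supply that.
- *That the artefact rivals the treatment effect.* An assumed shift of 0.1 to 0.3 SD would be 0.1/0.17 = 0.6 to 0.3/0.17 = 1.8 times the youth MI effect of d = 0.17 quoted under Significance. The shift is pure assumption, and d = 0.17 is a background meta-analytic figure, not this study's expected RAPI change.
- *That the synchrony association is biased.* That would need a RAPI-based model and a shift that varies with synchrony. The document gives neither.

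**Conclusion.** The point holds as a fault of timing and labelling in a declared primary outcome. As the detailed procedures stand, every participant assessed under them, up to the planned 248, lacks a RAPI from before the intervention. The overviews read naturally as the opposite order. Any RAPI change score or baseline adjustment would carry an error equal to the mean reporting shift, of unknown size and direction, with no control arm to remove it. The other alcohol and cannabis symptom measures in the battery share the problem.

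The conclusion rests on two readings: that the detailed items, not the overviews, describe what will be done, and that the TLFB is completed in its listed place before the session. On the second reading, the 12-month drinking-days model and the in-session feedback are not directly affected.

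**What to change.** Move the RAPI, the DSM-5 alcohol and cannabis criteria and the Cannabis Problems Questionnaire to the pre-session slot that holds the TLFB. The psychosocial scales that are not outcomes can stay after the session. Then make Study Design, the Participation Day overview, both Primary Measures paragraphs and the Baseline Behavioral Assessment item state this one order, and say outright that the TLFB precedes the session.

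If any RAPI has already been taken after a session, label it post-session in the data and do not use it as a pre-intervention baseline. If the sponsor keeps the present order on purpose, the minimum is to apply that same label to all of them and state how RAPI change will be assessed without a baseline.

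The cost is a reordering of REDCap forms, an amendment to the text, a somewhat longer assessment before the session, and some possible priming of session talk, which should be similar for all participants.
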